### **6.2.1 Local and Systemic Reactions**

The occurrence of selected indicators of reactogenicity (listed in Table 6.2.1) and other unsolicited adverse events will be recorded in the diary card by the subject and reported in the corresponding CRF.

### **6.2.2 Adverse Events**

An adverse event (AE) is defined as any untoward medical occurrence in a subject or clinical investigation subject administered a pharmaceutical product at any dose that does not necessarily have to have a causal relationship with this treatment. An AE can, therefore be any unfavorable and unintended sign (including an abnormal laboratory finding, for example), symptom, or disease temporally associated with the use of an investigational product, whether or not considered related to the investigational product. This definition includes intercurrent illnesses or injuries and exacerbation of pre-existing conditions.

An unexpected adverse event is one that is not listed in the current Summary of Product Characteristics or the Investigator's Brochure or an event that is by nature more specific or more severe than a listed event.

All AEs will be monitored until resolution or, if the AE becomes chronic, a cause identified. If an AE is unresolved at the conclusion of the study, a clinical assessment will be made by the investigator and medical monitor whether continued follow-up of the AE is warranted.

The severity of events reported on the "Adverse Events" CRF will be determined by the investigator as:

|           |                                                        |
|-----------|--------------------------------------------------------|
| Mild:     | transient with no limitation in normal daily activity. |
| Moderate: | some limitation in normal daily activity.              |
| Severe:   | unable to perform normal daily activity.               |

The relationship of the study treatment to an AE will be determined by the investigator based on the following definitions:

#### **1. Not Related**

The AE is not related to an investigational vaccine if there is evidence that clearly indicates an alternative explanation. If the subject has not received the vaccine, the timing of the exposure to the vaccine and the onset of the AE are not reasonably related in time, or other facts, evidence or arguments exist that strongly suggest an alternative explanation, then the AE is not related.

## 2. Possibly Related

The administration of the investigational vaccine and AE are considered reasonably related in time **and** the AE could be explained either by exposure to the investigational vaccine or by other causes.

## 3. Probably Related

Exposure to the investigational vaccine and AE are reasonably related in time and no alternative explanation has been identified.

The relationship of the study treatment to an AE will be determined by the investigator.

### 6.2.3 Serious Adverse Events

A serious adverse event (SAE) is defined as any untoward medical occurrence that at any dose:

- Results in death.
- Is life-threatening (i.e., the subject was, in the opinion of the investigator, at immediate risk of death from the event as it occurred); it does not refer to an event which hypothetically might have caused death if it were more severe.
- Requires or prolongs subject's hospitalization.
- Results in persistent or significant disability/incapacity (i.e., the event causes a substantial disruption of a person's ability to conduct normal life functions).
- Results in a congenital anomaly/birth defect.
- Requires intervention to prevent permanent impairment or damage.
- Is an important and significant medical event that may not be immediately life threatening or resulting in death or hospitalization but, based upon appropriate medical judgment, may jeopardize the subject or may require intervention to prevent one of the other outcomes listed above.

Grade 4 and 5 laboratory deviations are also considered SAEs.

Of note: a "possible vaccine failure" should be reported as a SAE only if it resulted in a laboratory confirmed infectious disease which should have been prevented by the vaccine implied.

Adverse events which do not fall into these categories are defined as **non-serious**.

It should be noted that a severe adverse event need not be serious in nature and that a serious adverse event need not, by definition, be severe.

In addition, a pre-existing event or condition that results in hospitalization should be recorded on the Medical History CRF. If the onset of an event occurred before the subject entered the trial (e.g., any pre-planned hospitalization for conditions like cosmetic treatments or for non-emergency routine visits for a pre-existing condition), the hospitalization would not lead to an AE being classified as serious unless, in the view of the investigator, hospitalization was prolonged as a result of participation in the clinical trial or was necessary due to a worsening of the pre-existing condition.

For instructions on SAE reporting, please refer to section 6.2.6.

#### **6.2.4 Subject's Diary Card**

Diary Cards will be completed by the subject and used by the study staff to record safety information (concomitant medications and vaccinations, local and systemic reaction, AE and SAE) occurring in the entire duration of the study (28 days).

According to ICH GCP guidelines 1.52, subject's Diary Card is a "Source Document". It is an investigator responsibility to ensure that data on the diary card correspond to the real health status of subject and to accurately transcribe data from the Diary Card to the CRF.

In case the Diary Card is not available, the study staff will document the reasons for the missing documents on the Comment section of the CRF and the CRF will be completed with UNK for all assessments. Nevertheless, if a SAE occurred it must be recorded in SAE form and in the adverse event section of CRF.

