**Number of Subjects planned:**  
A total of 88 subjects (22 for each of the four groups) are planned for enrolment into the study. Assuming a 10% drop out rate, there will be approximately 80 evaluable subjects (20 for each of the four study groups). Subjects withdrawn or lost to follow up will not be replaced.

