- Physical examination (including injection site or intended injection site) must be performed by a qualified health professional designated within the Site Responsibility Delegation Log. Complete physical examination will be performed at Day 1 and Day 28
- Data on local and systemic reactions will be collected by the study personnel for all subjects at 1 hour post-injection. Subjects will record local and systemic reactions on the diary card daily for 7 days after study vaccination
- On Day 8, collect all information on local or systemic reactions and adverse events (AEs) recorded in diary card on an ad-hoc form via a structured telephone call. The ad-hoc form will be kept as a source documentation for reconciliation with information in diary card brought in by the subject at Visit 2.
- Assess AEs and SAEs according to Safety Assessment Table (Table 6.2.1)
- Collect concomitant medications/vaccines according to Safety Assessment Table (Table 6.2.1)
- Any subject who terminates the study earlier is recommended to undergo study-termination procedures.

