### Day 8 Safety Phone Call

- Collect all information on local or systemic reactions and adverse events (AEs) recorded in the diary card on an ad-hoc form via a structured telephone call. The ad-hoc form will be kept as a source documentation for reconciliation with information in diary card brought in by the subject at Visit 2.

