**Table 6.2.1: Medical and Safety Assessments to be reported into CRF**

|                                   |                                                                                                                                                                                                                                                                 |
|-----------------------------------|-----------------------------------------------------------------------------------------------------------------------------------------------------------------------------------------------------------------------------------------------------------------|
| Before Visit 1 vaccination | Medical History:
Any significant past diagnoses in the last 12 months including injuries, hospitalizations, major surgeries, or other significant medical conditions which may impair the assessment of immunogenicity or safety of the study vaccine |
|                                   | Medications:
All vaccinations received in the 4 weeks before study vaccination.
All investigational products received during the previous 30 days                                                                                                  |

|                                                         |                                                                                                                                                                                                                                                                                                                                                                                                                                                                              |
|---------------------------------------------------------|------------------------------------------------------------------------------------------------------------------------------------------------------------------------------------------------------------------------------------------------------------------------------------------------------------------------------------------------------------------------------------------------------------------------------------------------------------------------------|

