#### **6.2.6 Methods and Timing for Assessing and Recording Safety Parameters**

The period of observation for adverse events starts from the time the subject receives the vaccination. All study subjects will be observed at site for at least 1 hour after vaccination for evidence of immediate reactions and in particular for symptoms of allergic phenomena (such as rashes or other allergic manifestations). Each subject will be instructed to complete a diary card for 28 days (duration of study) following vaccination, to describe local and systemic reactions (during the 7-day period after vaccination) and AEs/ SAEs (during the 28 days duration of the study).

On day 8, all information on local or systemic reactions and adverse events (AEs) recorded in the diary cards will be collected on an ad-hoc form via a structured telephone call. The ad-hoc form will be kept as a source documentation for reconciliation with information in diary card brought in by the subject at visit 2 (day 28).

All adverse events occurring within the above period, regardless of severity, will be monitored by the investigator until resolution. All subjects experiencing adverse events - whether considered associated with the use of the study vaccine or not - must be monitored until symptoms subside and any abnormal laboratory values have returned to baseline, or until there is a satisfactory explanation for the changes observed, or until death, in which case a full pathologist's report should be supplied, if possible. All findings must be reported on an "Adverse Events" CRF and on the "Vaccine Serious Adverse Event" form, if necessary. All findings in subjects experiencing adverse events must be reported also in the subject's medical records.

All SAEs which occur during the course of the trial, whether considered to be associated with the study vaccination or not, must be reported **within 24 hours** or at the latest on the following working day by telephone or fax to Novartis Vaccines Institute for Global Health. The "Vaccine Serious Adverse Event" form is to be completed for all SAEs and faxed to the sponsor.

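### When the diary card is missing, section 6.2.4 keeps the Day 1–7 reactions and non-serious adverse events already held on the Day 8 telephone form out of the CRF

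*Protocol*

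**What the plan says.** Section 6.2.4 (Subject's Diary Card) names the card as a source document and makes the investigator responsible for transcribing it accurately. If the card is not available, staff note the reason in the CRF comments and "the CRF will be completed with UNK for all assessments". One exception follows: "Nevertheless, if a SAE occurred it must be recorded in SAE form and in the adverse event section of CRF". Reactions and non-serious adverse events get no such exception.

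The Day 8 call in section 3.3 requires staff to "Collect all information on local or systemic reactions and adverse events (AEs) recorded in the diary card on an ad-hoc form". Section 6.2.6 repeats the step and gives the form its status: "The ad-hoc form will be kept as a source documentation for reconciliation with information in diary card". Reconciliation with the returned card is the only stated use. The card is collected at Visit 2 (Day 28, window +7), and the synopsis adds: "Subjects withdrawn or lost to follow up will not be replaced".

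Three other provisions bear on the rule:

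- The Appendix I footnotes state: "Data on local and systemic reactions will be collected by the study personnel for all subjects at 1 hour post-injection". Table 6.2.1, headed "Medical and Safety Assessments to be reported into CRF", has its own row for that hour.
- Section 3.3 has staff ask about adverse events at Visit 2 as a separate step from collecting the card.
- Section 6.2.6 requires what is found about adverse events to go on the Adverse Events CRF, whatever the severity.

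**The concern.** The solicited period is Days 1 to 7, and the Day 8 call follows directly after it. If the card has been filled in and the call takes place, the form can hold the subject's whole solicited record three weeks before the card is due. The form is most useful when the card never comes back, and in exactly that case section 6.2.4 gives it no role.

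The rule acts at data entry. A value entered as UNK does not reach the analysis database, so a later analysis plan working from that database cannot restore it. The rule also conflicts with section 6.2.6: a non-serious adverse event known from the call should go on the Adverse Events CRF under one section and be UNK under the other.

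Rates of post-vaccination reactions and adverse events are what the safety objective measures (section 2.1). Higher local reactogenicity of the conjugate in Phase 1 is part of the stated reason for testing lower doses (section 1.0). With 22 subjects per group, one subject is 1/22 = 4.5 percentage points.

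**Working it through.** **Who is affected.** The rule loses documented Day 1–7 data only where two things are both true: the Day 8 call took place, and the card was never obtained.

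| Situation | Day 8 form held | Card held | Day 1–7 data lost through the rule |
|---|---|---|---|
| Card returned | either | yes | no |
| Left before Day 8, no card | no | no | no: there is no form to use |
| Call done, card never obtained | yes | no | yes |

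**Inputs.** 22 vaccinated per group, and 10% drop-out leaving about 20 (synopsis and section 3.2.2). The number of missing cards is not in the protocol; 1, 2 and 4 per group are assumed. The drop-out figure gives 22 × 0.10 = 2.2, or about 2. That is an upper illustration, because some drop-outs leave before Day 8 and some may hand in the card.

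**The plan's nearest figure.** Section 7.2 states a 90% chance of seeing at least one subject with an event whose true rate is 10.9%, with 20 subjects. The formula is 1 − (1 − p)^n, and 1 − 0.891^20 = 90.1%, so the figure reproduces.

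**Precision, if loss is unrelated to reactions and UNK is excluded.**

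- Chance of seeing at least one such event: n = 22, 1 − 0.891^22 = 92.1%; n = 21, 91.1%; n = 20, 90.1%; n = 18, 87.5%.
- Standard error of a 50% rate, √(0.25/n): n = 22, 10.7 points; n = 20, 11.2 points.

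The sample-size section already works with n = 20. Losing two of 22 therefore does not take the trial below its stated precision; it gives up precision that the data held could have supplied.

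**Possible bias, at the extremes.** With N = 22, R true reactors and m missing cards:

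- all missing are reactors, UNK excluded: (R − m)/(N − m)
- all missing are non-reactors, UNK excluded: R/(N − m)
- all missing are reactors, UNK counted as no reaction: (R − m)/N

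| True rate | m | Reactors lost, excluded | Non-reactors lost, excluded | Reactors lost, UNK as none |
|---|---|---|---|---|
| 11/22 = 50.0% | 1 | 10/21 = 47.6% | 11/21 = 52.4% | 10/22 = 45.5% |
| | 2 | 9/20 = 45.0% | 11/20 = 55.0% | 9/22 = 40.9% |
| | 4 | 7/18 = 38.9% | 11/18 = 61.1% | 7/22 = 31.8% |
| 6/22 = 27.3% | 1 | 5/21 = 23.8% | 6/21 = 28.6% | 5/22 = 22.7% |
| | 2 | 4/20 = 20.0% | 6/20 = 30.0% | 4/22 = 18.2% |
| | 4 | 2/18 = 11.1% | 6/18 = 33.3% | 2/22 = 9.1% |

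The error can go either way. If the Day 8 forms are entered, these subjects stay in both numerator and denominator and the distortion disappears for the data held. Safety is descriptive with no inference (sections 7.1 and 7.6.2), so neither alpha nor power is at stake.

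**The case against.** The best defence of the rule is data quality. The card is the named source and the telephone form was designed only as a cross-check. A cautious sponsor may prefer not to enter values that cannot be verified against the card. That is a respectable preference, but the protocol itself calls the form source documentation, and a source flag would show which values came from it. The objection stands as a downside of the change, not as a reason to discard the data.

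Several stronger readings are tempting, and the text does not carry them.

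- **That the 1-hour findings are lost too.** A reader might take all assessments literally. The sentence sits in the diary section, straight after the duty to transcribe the card. Read literally it would also blank the physical examination and pregnancy test, which cannot be meant. The 1-hour reactions are collected by staff and have their own row in Table 6.2.1. The wording should be tightened, but loss of these data is not established.
- **That all non-serious adverse events disappear.** A subject who attends Visit 2 without the card is still asked about them by staff. The conflict with section 6.2.6 matters mainly for subjects who never attend Visit 2.
- **That about two per group will be affected.** The 10% is a drop-out assumption, not a rate of card loss. The Appendix I footnotes also recommend termination procedures for subjects who leave early, which may recover some cards.
- **That reaction rates will be biased.** There is one injection and so no later dose to avoid. Section 3.2 says that in earlier conjugate studies most reactions began within 2 days and lasted no more than 4. Loss after Day 8 would have to depend on reactions that had mostly resolved. Nothing in the protocol shows that, and the rule is the same in all four blinded groups.

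**Conclusion.** The point holds for subjects with a Day 8 form and no card. For them section 6.2.4 keeps documented Day 1–7 reactions and non-serious adverse events out of the CRF, and it sits badly with the reporting duty in section 6.2.6. The source records remain at the site; what is lost is their place in the analysed data.

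The certain effect is some loss of precision, and it is small: with two subjects lost of 22, the standard error of a 50% rate rises from 10.7 to 11.2 points. Bias is possible, not shown. In the worst case with two lost, a 27.3% rate is reported as 20.0% (UNK excluded) or 18.2% (UNK counted as none). Those figures rest on an assumed number of missing cards, and on every missing subject having reacted.

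This should be fixed because the data exist and the correction is easy. It does not call the design or the sample size into question.

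**What to change.** Amend section 6.2.4 in three respects:

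1. When the card is unavailable, transcribe Day 1–7 reactions and adverse events from the Day 8 form into the CRF, with a flag that the source is the telephone form.
2. Use UNK only for items that no other source holds, such as card entries made after the call.
3. State that the UNK rule does not reach data collected by staff, including the 1-hour assessment and adverse events ascertained at Visit 2. This removes the literal reading and the conflict with section 6.2.6.

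Sections 3.3 and 6.2.6 should then say that the Day 8 form also serves as the source when no card is obtained. How UNK subjects count in denominators, and any listing by source, can be left to the statistical analysis plan.

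The cost is one paragraph of protocol text, matching CRF completion instructions and one flag field, with no added visits, staff or burden on subjects. The downside is that the flagged values will not have been reconciled with the card.

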#### **6.2.5 Pregnancies**

To ensure subjects' safety, each pregnancy in a subject on study vaccine must be reported to Novartis Vaccines Institute for Global Health within 24 hours of learning of its occurrence. The pregnancy should be actively followed up to determine outcome, including spontaneous or voluntary termination, details of the birth, and the presence or absence of any birth defects, congenital abnormalities, or maternal and/or newborn complications.

Any SAE experienced during pregnancy must be reported on the SAE Report Form.

#### **6.2.6 Methods and Timing for Assessing and Recording Safety Parameters**

The period of observation for adverse events starts from the time the subject receives the vaccination. All study subjects will be observed at site for at least 1 hour after vaccination for evidence of immediate reactions and in particular for symptoms of allergic phenomena (such as rashes or other allergic manifestations). Each subject will be instructed to complete a diary card for 28 days (duration of study) following vaccination, to describe local and systemic reactions (during the 7-day period after vaccination) and AEs/ SAEs (during the 28 days duration of the study).

On day 8, all information on local or systemic reactions and adverse events (AEs) recorded in the diary cards will be collected on an ad-hoc form via a structured telephone call. The ad-hoc form will be kept as a source documentation for reconciliation with information in diary card brought in by the subject at visit 2 (day 28).

All adverse events occurring within the above period, regardless of severity, will be monitored by the investigator until resolution. All subjects experiencing adverse events - whether considered associated with the use of the study vaccine or not - must be monitored until symptoms subside and any abnormal laboratory values have returned to baseline, or until there is a satisfactory explanation for the changes observed, or until death, in which case a full pathologist's report should be supplied, if possible. All findings must be reported on an "Adverse Events" CRF and on the "Vaccine Serious Adverse Event" form, if necessary. All findings in subjects experiencing adverse events must be reported also in the subject's medical records.

All SAEs which occur during the course of the trial, whether considered to be associated with the study vaccination or not, must be reported **within 24 hours** or at the latest on the following working day by telephone or fax to Novartis Vaccines Institute for Global Health. The "Vaccine Serious Adverse Event" form is to be completed for all SAEs and faxed to the sponsor.

### Post-Study Events

Any SAE occurring at any time after the end of the study and considered to be caused by the study vaccine - and therefore a possible adverse reaction - must be reported by using a SAE Report Form to:

